The result variables of the intervention will be the following: (a) change in knowledge of sexuality manage correctly information on topics related to the biological components of sexuality such as reproduction, prevention of STI and pregnancy, among others; (b) change in preventive sexual behavior, which may be related to (i) behavior or intention to prevent STI and pregnancy, or (ii) sexual abstinence or intention to postpone initiation of sexual life; (c) change in gender attitude related to (i) positive disposition towards persons of different genders and sexual orientation, and (ii) empowering in sexuality of LGBT and female students; (d) change in components of mental health related to sexual health, decrease of internalizing-externalizing symptomology, and improvement in self-efficacy (Table 2). The following instruments will be used:*Knowledge test* [33]. This is a 34-item multiple choice instrument which was designed to evaluate the effectiveness of interventions in sexual education to improve knowledge on sexuality in adolescents; it evaluates areas including pregnancy, STI, physical development, and others. Its reliability is *α* = 0.89.*Ad hoc survey*. It was elaborated by the research team to evaluate the behavior and intention of preventive behavior in sexuality, self-efficacy. and empowerment in sexuality in LGTB and female students. Ad-hoc surveys have been used and reported in other randomized controlled trial of interventions in sexual health (e.g.. Coyle [34], Goesling [35]. and Yakubu [36]). This survey will follow the guidelines developed by Manaseri [37] and Jirapongsuwan [38].*Scale for detection of sexism in adolescents (DSA)* [39]. This is an instrument of 26 items developed for adolescents. It evaluates sexism (attitude of superiority towards women), differentiating between hostile and benevolent sexism. The response scale for the items is a Likert type with six alternatives (from 1 = disagree completely to 6 = agree completely). Its reliability is *α* = 0.881.*Scale of negative attitudes toward trans persons (NATP)* [40]. It measures attitude as an expression of prejudice towards trans persons. It has nine items with a Likert scale with five response options, from 1 = disagree completely to 5 = agree completely. Its reliability is *α* = 0.886.*Short version of modern homophobia scale* [41]. It measures homophobic attitudes in the dimensions of personal discomfort, institutional, and deviation/changeability. It is composed of 46 items that evaluate attitudes towards lesbians and gays on a Likert scale of 1–5. Its reliability is *α* = 0.80.*Pediatric symptom checklist (PSC-17)* [42]. This is an abbreviated version of the 35-item PSC [43]. It evaluates general psychosocial functioning, detecting emotional and behavioral difficulties in children and adolescents [44]. Its reliability is *α* = 0.72. PSC-17 is self-administered by adolescents, evaluating the existence of internalizing difficulties (e.g., despair and sadness), externalizing difficulties (e.g., difficulties in social relations such as disobedience of norms and fights with others), and attention difficulties (e.g., difficulty in concentration -60,66-). As in other studies (e.g., Penner [45]), this instrument will be used to evaluate the adolescents’ mental health. The baseline and follow-up evaluations will be obtained confidentially, and be recorded in files managed by the team responsible for the study.

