### Analytical methods

The information that results from the application of the scales will be summarized with descriptive statistics (frequency table, mean, standard error, and asymmetry coefficient) for the pre- and post-intervention evaluations.

Since the intervention has specific objectives for each session, it is not appropriate to impute missing data. However, to account for the potential lack of adherence by some students, it is suggested that participants who miss more than 30% of the sessions should not be included in the data analysis. Regardless of attendance, students will be able to participate in all workshop activities.

We will compare the three evaluations, incorporating information relative to the type of school and course. If the data are normally distributed, we will perform one-way ANOVAs, incorporating post hoc information of the results when necessary, and perform pair-wise comparisons using the Tukey or Games-Howell test.

After the variables with main effects are established, we will perform a factorial ANOVA, in which one of the factors will be fixed (i.e., type of school) and the other will be the repeated measures of the three evaluations. As well as evaluating if the main effects are sustained over time, this will evaluate possible interactions among the studied factors. In this case, following the guidelines proposed by Cohen^75^ for ANOVAs with two or more factors, the effect size will be reported as the partial Eta^2^ statistic. The interpretation of the effect sizes will consider the suggestions of Cohen [50]. These analyses will use the program Jamovi version 1.2 [51].

No interim data analysis will be conducted, and there will be no stopping guidelines.

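### The first-stage ANOVAs are conditional on normal data, so the choice of test depends on the data outcome by outcome, for no statistical gain

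*Protocol article*

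**What the plan says.** The Analytical methods section of the protocol article compares the three evaluations under a condition: "If the data are normally distributed, we will perform one-way ANOVAs". Where needed, the authors will "perform pair-wise comparisons using the Tukey or Games-Howell test". A second analysis comes next: "After the variables with main effects are established, we will perform a factorial ANOVA", with type of school and the repeated evaluations as factors and partial eta squared as effect size. That second step has no normality condition of its own, but it begins from what the first step found.

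The Outcomes section describes the measures:

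- Knowledge: "This is a 34-item multiple choice instrument".
- Sexism scale (26 items): "The response scale for the items is a Likert type with six alternatives".
- Attitudes toward trans persons: "It has nine items with a Likert scale with five response options".
- Mental health: a 17-item symptom checklist.
- Behaviour: a survey written by the team "to evaluate the behavior and intention of preventive behavior in sexuality", covering "behavior or intention to prevent STI and pregnancy, or (ii) sexual abstinence or intention to postpone initiation of sexual life". Its response format is not given.

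The Sample size section rests power on an analysis of variance with 605 students. The Allocation process section keeps group membership from the analyst.

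**The concern.** A rule that allows the ANOVA only when the data are normal makes the test for each outcome depend on what the data look like. That would be defensible if the condition protected the inference. With about 300 students per arm it protects little, because a comparison of means is robust to the shapes these scales produce. A formal normality test at that size detects departures that do not matter. The choice between Tukey and Games-Howell does not help, since it concerns equal or unequal variances and not shape.

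Two things are at stake. First, different outcomes, and so different hypotheses, could be tested by different methods chosen after a look at the data. Second, where the condition fails, the test used is no longer the one for which the trial was sized.

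**Working it through.** **The plan's own figures.** This point disputes none of them. With z = 2.58, p = 0.5 and a 5% margin, n0 = 2.58² × 0.25 / 0.05² = 665.64. The finite-population correction gives 665.64 / (1 + 664.64/6518) = 604.0, against 605 stated. The power of at least 0.8 can be neither confirmed nor refuted, because no SD is given for the 0.2-point difference. With 302.5 per arm, two-sided power is 0.69 if the SD is 1 and 0.81 if it is 0.87. What matters here is that the figure belongs to an analysis of variance.

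**Does the condition fail, and does failure matter?** The document gives no score distributions and names no normality test, so both are assumptions here.

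- Test: Shapiro-Wilk at 0.05.
- Samples: 301 against 308 independent students (the totals of Table 1), no true difference, 2,000 runs per shape.
- Scales: one common factor, loading 0.6, item SD one quarter of the response range, rounded and cut off at the ends. The item mean below is the value before rounding. The checklist is taken as scored 0-2.
- Knowledge: binomial with 34 items, with the student's logit drawn with SD 1.
- Factor: study group. The section does not name the factor of the one-way ANOVA.

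| Assumed shape | Mean skewness | Rejected, pooled residuals (609) | Rejected, one arm (301) | ANOVA type I error |
|---|---|---|---|---|
| Sexism scale, item mean 3.5 (centred) | 0.00 | 15% | 7% | 0.051 |
| Sexism scale, item mean 2 | 0.57 | 100% | 100% | 0.046 |
| Sexism scale, item mean 1 | 1.29 | 100% | 100% | 0.049 |
| Trans-attitude scale, item mean 3 (centred) | 0.00 | 39% | 24% | 0.057 |
| Trans-attitude scale, item mean 1.5 | 0.79 | 100% | 100% | 0.043 |
| Checklist, item mean 0.7 | 0.07 | 98% | 75% | 0.048 |
| Checklist, item mean 0.3 | 0.71 | 100% | 100% | 0.052 |
| Knowledge, mean logit 0.2 | -0.14 | 100% | 100% | 0.056 |
| Knowledge, mean logit 1.3 | -0.90 | 100% | 100% | 0.044 |
| Single 1-5 item, mean 3.5 | -0.22 | 100% | 100% | 0.043 |
| Yes/no item, 30% | 0.88 | 100% | 100% | 0.041 |

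The Monte Carlo standard error of a 0.05 error rate is √(0.05 × 0.95 / 2000) = 0.005. Two standard errors either side give 0.040 to 0.060, and every value in the last column lies inside that range.

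Three things follow. Skewed scores fail almost every time. Two nearly symmetric cases (knowledge at mean logit 0.2, checklist at 0.7) fail nearly as often on pooled residuals, so skewness alone does not decide the result. The answer also changes with how normality is checked: the checklist at 0.7 fails in 98% of samples on pooled residuals and 75% in one arm. In no case does failure signal a faulty ANOVA error rate.

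This last result concerns the shape of the scores only. Clustering by school was left out and is a separate matter.

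**The case against.** The strongest reply has four parts.

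1. *A condensed article may leave the normality criterion and the fallback to an analysis plan that is not shown.* This stands as far as it goes: the absence of a fallback is not the finding. The finding is the rule that is stated. A fallback written elsewhere would still be reached through a data-dependent gate.

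2. *The analyst is blind to group, so the test cannot be chosen on the results.* This largely stands. A reader might infer that the test would be picked from unmasked results; the Allocation process section does not support that. Some risk remains. Coded groups still show whether a difference is significant under each candidate test. The exclusion of students who miss more than 30% of sessions could also reveal the arm to whoever applies it, because controls attend no sessions.

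3. *No formal normality test is planned.* Correct. The only shape measure listed is the asymmetry coefficient. If normality is judged by that or by plots, the rejection rates above do not apply, and the rule then rests on judgement without a stated threshold.

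4. *A factorial ANOVA is also planned.* Correct, so a reader who takes the conditional step to be the only planned comparison goes too far. The second analysis nevertheless depends on the first.

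A reader might also infer that behaviour is recorded as yes or no, leaving the second hypothesis without a valid planned test. The survey's response format is not given, so this holds only for items that turn out to be binary.

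**Conclusion.** The point holds as a poorly chosen rule that should be changed. The condition governs the first-stage ANOVAs and, through them, the factorial ANOVA. Under a formal test on pooled residuals and the assumed shapes, it would fail in about 98-100% of samples for skewed scales, knowledge and the checklist, and in 15-39% for mid-centred attitude scales. It is therefore not true that every bounded scale would almost always fail. The homophobia scale was not simulated.

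The harm is an outcome-by-outcome choice of test that depends on the data and may replace the analysis on which power was based. It is not that ANOVA is invalid for these scores: its error rate stayed at 0.041-0.057 with independent students. Nor was any inflation of the error rate from selective choice calculated, so the documents and the working support a risk and not a demonstrated excess of false positives.

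**What to change.** Delete the normality condition and fix one model per outcome type before the data are seen.

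- **Scores:** a linear mixed model for the two evaluations after baseline, with arm, time, arm-by-time and baseline score, school as a random effect, and correlation between a student's repeated scores. Use a small-sample correction for 10 schools and check the model on its residuals. School belongs in the model because Table 1 places each school wholly in one arm.
- **Any survey item that proves to be binary:** the logistic counterpart.
- **Distribution-free check, if wanted:** permute arm over schools within the allocation scheme actually used. An unrestricted 5/5 split gives 10!/(5! × 5!) = 252 allocations. If assignment was restricted by the two size blocks in the Randomization section, there are fewer. For example, blocks of 4 and 6 schools split evenly (an assumption, as block sizes are not given) would give 6 × 20 = 120.

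The cost is a few sentences in Analytical methods, slightly more analysis work, and a software module beyond the basic ANOVA menu.

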**Methods:**

We will use a mixed method experimental design with a parallel cluster-randomized trial (GRTs) that will evaluate the effectiveness of a comprehensive gender-transformative intervention of sexual education (ENFOCATE -Focus-on-), which will be complemented with qualitative studies to understand the implementation process. The participants will be 609 10^th^ and 11^th^-grade students. The randomization will be by grade, and the data will be collected at three moments (pre-intervention, post-intervention, and a 3-month follow-up).

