### Sample size

There are currently 6518 students enrolled in the 10^th^ and 11^th^ grades in State-financed schools in the commune of Santiago. Using a 99% confidence level and a 5% error margin, the sample framework is 605 students, which will be divided into the study and control groups. The statistical power is determined using an analysis of variance with a significance level of 0.05, a sample size of 605 and an expected difference of 0.2 points between groups, which will provide a statistical power of at least 0.8. The 0.2 difference is the smallest reported in previous studies comparing the scores of two groups with the instruments that will be used; it was reported in the analysis of the scores of the scale of ambivalent sexism [24].

The statistical power was calculated using the software G*Power [25]. After making a slight adjustment due to the number of students currently enrolled in each school at each level, the definitive size of the experimental phase of the study will be 609 students.

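### The analysis reads as a main-effect screen ahead of the only step that can hold an interaction; because the programme effect is arm by time, the screen costs power

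*Protocol article*

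**What the plan says.** Protocol article, Analytical methods, sets out two steps.

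- Step one: "We will compare the three evaluations, incorporating information relative to the type of school and course". The test is conditional on distribution: "If the data are normally distributed, we will perform one-way ANOVAs", followed by Tukey or Games-Howell pairwise comparisons.
- Step two: "After the variables with main effects are established, we will perform a factorial ANOVA". Its factors are described thus: "one of the factors will be fixed (i.e., type of school) and the other will be the repeated measures of the three evaluations". Of this model the section says that "this will evaluate possible interactions among the studied factors", and that it will show whether main effects last over time.

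Trial arm is not named as a factor in either step. No sentence says that every outcome reaches step two whatever step one shows.

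Elsewhere, the Abstract states that "the data will be collected at three moments (pre-intervention, post-intervention, and a 3-month follow-up". The Outcomes section words each outcome as a change, beginning with "change in knowledge of sexuality". The Objectives section places the hypothesised effects in the experimental group. The Sample size section powers "an analysis of variance with a significance level of 0.05" on a difference of 0.2 points between groups.

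**The concern.** With a baseline and two later measurements in two arms, the programme effect is the extent to which the arms diverge after baseline. That is an arm-by-time interaction, and a one-way ANOVA cannot contain one. A main effect of time pooled over arms is a different quantity:

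- a gain in one arm only is roughly halved in the pooled mean;
- opposite movements in the two arms cancel;
- change common to both arms (maturation, retesting) counts in full.

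A main effect of arm averaged over all three evaluations is closer to the target, but the baseline, where no effect can exist, dilutes it.

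If outcomes must pass such a test before interactions are examined, some real programme effects are set aside before the one step that could show them. Which outcomes get that far then depends partly on change that has nothing to do with the programme.

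**Working it through.** **The plan's own figure.** The protocol gives no power for this two-step sequence. Its general statement is power of at least 0.8 with 605 students and a 0.2-point difference; no SD is given. With SD 1 and 302.5 per arm, the two-sided power of a simple two-group comparison is 0.69. Power of 0.8 needs a standardised difference of 2.80 × √(2/302.5) = 0.228, so an SD of at most 0.2/0.228 = 0.88. This only sets the scale; the point does not depend on it.

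**Inputs.** From Table 1: 301 study and 308 control students. From the protocol: three evaluations and alpha 0.05. Assumed: SD 1, equal within-student correlation ρ of 0.5 to 0.6, no clustering, no dropout, effect equal at post and 3 months.

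**Direct arm comparison of change** (mean of the two follow-ups minus baseline), gain 0.2 v 0:
- SE² = 1.5(1−ρ)(1/301 + 1/308), with 1/301 + 1/308 = 0.006569.
- ρ = 0.5: SE = 0.0702, z = 0.2/0.0702 = 2.85, power = Φ(2.85 − 1.96) = 0.81.
- ρ = 0.6: SE = 0.0628, z = 3.19, power = 0.89.
- Simulation gives 82–90%.

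**Time screen, arms pooled.**
- Pooled shift = 0.2 × 301/609 = 0.0989.
- Repeated-measures noncentrality = 609 × 0.0989² × (2/3)/(1−ρ) = 7.9 (ρ = 0.5) or 9.9 (ρ = 0.6). The pass rate is 0.71 or 0.81.
- An ordinary one-way ANOVA treats the three evaluations as independent, so its F is about (1−ρ) times the repeated-measures F. To exceed a critical value near 3.0, the latter must exceed about 3.0/0.5 = 6.0 or 3.0/0.4 = 7.5. Simulated pass rates are about 31% and 27–28%.
- With nearly equal arms, the pooled change and the arm difference in change are almost independent, so power after the screen is close to the product. One-way: 0.31 × 0.82 = 0.25 and 0.28 × 0.90 = 0.25. Repeated measures: 0.71 × 0.82 = 0.58 and 0.81 × 0.90 = 0.73. Simulation agrees.

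**Arm screen.**
- Averaged over three evaluations, 0.2 becomes 0.2 × 2/3 = 0.133. With SE = √[(1+2ρ)/3 × 0.006569] = 0.066 (ρ = 0.5) or 0.069 (ρ = 0.6), z is 2.01 or 1.92 and about half of such outcomes pass.
- At post only: SE = √0.006569 = 0.081, z = 2.47, pass rate 0.69.

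**Power for study +0.2 SD, control flat (simulation, ρ 0.5–0.6):**

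| Route to the arm comparison | Power |
|---|---|
| No screen | 82–90% |
| One-way time screen, as written | about 25% |
| Repeated-measures time screen | 59–73% |
| Arm main effect averaged over time | 41–44% |
| Arm difference at post | 58–65% |

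With 3,000 runs the simulation error is up to about 2 × √(0.25/3000) = 0.018. If step two is instead the two-degree-of-freedom arm-by-time F test (ρ = 0.5), power is 72% without a screen, 52% after the repeated-measures screen and 23% after the one-way screen.

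**Other patterns.**
- Study +0.3, control flat: the repeated-measures screen drops about 1–3% of outcomes, the one-way screen about 18%.
- Study +0.1, control −0.1: the pooled shift is (0.1 × 301 − 0.1 × 308)/609 = −0.001. The repeated-measures screen passes about 5% and the one-way screen under 1%, although the direct comparison has 80% power or more.
- Both arms +0.15, no programme effect: a time screen passes about 82–99%; a later arm comparison flags about 5%.

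**The case against.** **The screen is inferred.** The text does not say that only some outcomes proceed, and variables with main effects could mean factors, such as school type or course, that are then carried into a factorial model. On that reading no outcome is dropped and the power loss does not arise. The wording does not exclude this. But the sentence follows one-way tests of the scales across evaluations and leads into a model meant to show whether those effects last, so a screen on outcomes is the more natural reading. If it was not intended, removing the clause costs nothing.

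**The screen may compare groups rather than times.** Asking whether an effect lasts over time suits a between-group effect better, and the power statement concerns a group difference. This has force. With the arms compared at either follow-up, the +0.1/−0.1 case passes in 78–85% and change shared by both arms in only 7–10%. A cost remains: 41–65% power against 82–90% in the one-arm case.

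**Stronger readings that a reader might infer.**
- That nearly all real effects are lost: this needs a time screen and controls that worsen about as much as the study arm improves. The protocol hypothesises improvement in the experimental group and predicts no decline in controls.
- That shared change yields false programme claims: a correct arm comparison afterwards still errs in about 5%. The risk arises only if step two does not test arm by time.
- That outcomes failing the screen go unreported: the section does not say so, and it promises descriptive statistics for the scales without any screen.

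**The article is condensed and an analysis plan may exist.** The sequence is stated, not left out, so a later plan would have to depart from it.

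**Conclusion.** The concern holds as a loss of power from a stated sequence that reads most naturally as a main-effect screen. At a 0.2 SD gain in the study arm with control flat, every version of an outcome screen that was checked lowers the chance of finding the effect, most of all the one-way time comparison as written. The loss depends on the pattern of change: with a repeated-measures screen it is small at 0.3 SD, and with a time screen it is near total only when the arms move in opposite directions.

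Whether shared change could be taken for a programme effect turns on step two. The section names school type and evaluation as its factors, not arm, so an arm-by-time test is not secured. If school type was meant to stand for arm, the right interaction is present, but the screen still precedes it.

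The sizes rest on the assumed SD, correlation and absence of clustering. Whole courses in 10 schools are allocated, so the absolute powers do not describe this trial; clustering would lower them without changing the mechanism.

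**What to change.** In Analytical methods, delete the opening condition that makes the factorial ANOVA follow from established main effects. State instead that one prespecified arm comparison of change from baseline (arm by time, at post and at 3 months) is run for every outcome listed in the Outcomes section, and that all results are reported whatever the main effects show. Name trial arm explicitly as a factor in that model.

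The cost is one sentence of text and a few more model runs. No additional data or students are needed.

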### Objectives of the study

The main objective of this study is to evaluate the effectiveness of a preventive-comprehensive program of sexual education in schools directed to students, using a mixed experimental design [23].

Given that comprehensive programs of sexual health have more effective results in attitudes and knowledge, and that a program that incorporates a gender-transformative perspective contributes to equity in sexual health, we hypothesize that the intervention designed and implemented in the experimental group: (i) will increase their sexuality knowledge level; (ii) will increase their preventive sexual behavior (or intentions); (iii) will favor a gender-positive attitude; and (iv) will decrease internalizing and externalizing problems and attention in mental health. The secondary objective is to examine the implementation intervention process, that is, identify the strengths and obstacles in the real context in which the study intervention is performed, to understand the determinants and strategies of the success of the implementation.

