## Methods

### Trial design

We propose a mixed method experimental design [23] with a parallel cluster-randomized trial (GRTs) that will evaluate the efficiency of intervention and implementation of a comprehensive gender-transformative sexual education, along with qualitative studies to understand the implementation process. The results of the intervention will be evaluated after it finishes, and in a 3-month follow-up. Each participant will be sent a link to the questionnaire (web-based survey). Follow-up contact will be done with WhatsApp or telephone calls. The protocol of the study is drafted following the Standard Protocol for a randomized trial of a social or psychological intervention (CONSORT-SPI). Figure 1 is a general flow chart of the procedure (supplementary material 1 includes the SPIRIT checklist).

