### Participants: eligibility criteria

The intervention will be directed exclusively to students of the 10^th^ and 11^th^ grades who are enrolled in one of the education establishments that depend on the Municipality of Santiago. The inclusion criteria for these schools will be the following: (i) have students of these grades enrolled; (ii) not being an education center oriented to adults or persons deprived of liberty (e.g., closed or semi-closed compounds of Gendarmería de Chile or the National Service for Minors); (iii) have regularity in teaching and learning (for example, schools that were not partially interrupted in 2022 by student manifestations); and (iv) have informed consent of the director. The inclusion criteria for the students will be (i) having 90% or greater attendance in classes: (ii) providing informed consent of voluntary participation; and (iii) having explicit and informed consent of their parents or guardians.

The selected students will be randomly divided into the study and control groups; the intervention will take place in the same schools that the students attend. The assignment to groups will use simple random sampling, performed in two stages. In the first stage, the available schools will be randomly assigned to the study and control groups, while the second stage will randomly select the groups in each school that will participate. The study groups will receive a 10-session intervention in sexual education, covering topics related to preventive sexual conduct, gender equity, and mental health. The control groups will not receive intervention; they will continue with the sexual orientation that each school provides to its students. Sexual orientation is general and is provided by the Ministry of Education. The goal is to evaluate and diagnose the behaviors and reproductive health needs of adolescents, addressing the values adopted regarding the decision to engage in sexual relationships and/or have multiple sexual partners, as well as perceptions of risk.

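### No planned analysis names study versus control or arm × time, so on the plain reading the effectiveness hypothesis is not tested

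*Protocol article*

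**What the plan says.** The Objectives section puts the question in terms of the programme's effect: "we hypothesize that the intervention designed and implemented in the experimental group" will improve knowledge, preventive behaviour, gender attitude and mental health. Trial design calls the study a "parallel cluster-randomized trial (GRTs) that will evaluate the efficiency of intervention", and the eligibility section states that "the available schools will be randomly assigned to the study and control groups". The Sample size section bases power on an ANOVA for a difference between groups.

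Analytical methods then sets out two steps.

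- Step 1: "We will compare the three evaluations, incorporating information relative to the type of school and course". The test is given next: "If the data are normally distributed, we will perform one-way ANOVAs, incorporating post hoc information of the results when necessary", with Tukey or Games-Howell pairwise comparisons.
- Step 2: "After the variables with main effects are established, we will perform a factorial ANOVA". In it, "one of the factors will be fixed (i.e., type of school) and the other will be the repeated measures of the three evaluations". Besides asking whether main effects last, "this will evaluate possible interactions among the studied factors".

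Study versus control is named in neither step.

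**The concern.** In a parallel trial with baseline and two later measurements, the effectiveness question is answered by the difference between arms in change from baseline: arm × time, or the arm difference adjusted for baseline. A test over time alone also picks up maturation, repeat testing and ordinary schooling, which both arms share. A type of school × time test asks whether kinds of school change differently, which is another question unless type of school is the arm.

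The order of the steps adds to this. A programme that works shows as an interaction between arm and time, and a screen on main effects is poorly placed to find one. The plan could therefore report shared change as success and pass over an outcome on which the programme worked.

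This is not detail left to a separate analysis plan. The article fixes the factors, the order, the post hoc tests, the effect-size measure and the software, and what it fixes does not match its own hypothesis.

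**Working it through.** **Question against model terms.**

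| Needed for the hypothesis | Where Analytical methods supplies it |
|---|---|
| Arm (study or control) | Not named |
| Time (three evaluations) | Named in both steps |
| Arm × time | Not named; interactions are among the studied factors, stated as type of school and time |

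The only classification of schools that the article defines apart from arm is the pair of size blocks under Randomization.

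**The plan's own figures.** Analytical methods gives no number to reproduce. The power statement (605 students, difference of 0.2 between groups, power at least 0.8) can be met under some readings of the 0.2 and does not bear on this point.

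**Inputs for an illustration.** From Table 1: 301 study and 308 control students, 609 in all. Assumed, because the documents do not give them: SD 1, within-student correlation ρ, a change of 0.2 SD present at both later evaluations, no clustering, test level 0.05.

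**Type of school × time when school type is unrelated to arm** (pre to post, ρ = 0.5, 2,000 simulated trials):

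- True arm effect 0.2 SD, no shared change: school type × time rejects in 5.2%, which is just the test level; arm × time rejects in 70.5%.
- No arm effect, shared change 0.2 SD: a paired test of time, pooled over arms, rejects in 99.9%; arm × time rejects in 5.3%.

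**Step 1 read as an unpaired one-way ANOVA over the three evaluations, pooled over arms.** Two things weaken it against a true arm effect.

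1. Pooling dilutes the effect: 0.2 × 301/609 = 0.099 SD.
2. Ignoring the pairing inflates the standard error. Take ρ = 0.6. The unpaired SE of a difference between two evaluations is √(2/609) = 0.057. The correct paired SE is √(2(1 − 0.6)/609) = 0.036.

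So 0.099/0.057 = 1.7, against 0.099/0.036 = 2.7 with pairing. For the arm difference in change, the SE is √(2(1 − 0.6)(1/301 + 1/308)) = 0.072, and 0.2/0.072 = 2.8.

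Simulated rejection rates under this reading:

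| Situation | Unpaired test over time | Arm difference in change |
|---|---|---|
| True 0.2 SD effect, no drift, ρ = 0.6 | about 27 to 29% | 78% |
| Same, ρ from 0.3 to 0.7 | 37% falling to 24% | 55% rising to 89% |
| Same, ρ = 0.8 | about 18% | not needed here |
| No effect, shared 0.2 SD drift, ρ from 0.3 to 0.7 | 98 to 99.9% | about 5% |
| No change at all, ρ from 0.3 to 0.7 | 0 to 1.4% | about 5% |

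**Other readings of step 1, true 0.2 SD effect, ρ = 0.6.** A paired test over time passes in about 81%. A one-way ANOVA by arm at post-intervention passes in about 69%. The size of the loss therefore depends heavily on which test is meant.

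**The case against.** The strongest defence is that a comparison between arms is clearly intended and the text is merely loose. Four arguments support it.

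- **Type of school may mean study or control school.** Schools are the units assigned, and each school in Table 1 lies wholly in one arm. On that reading the factorial model is arm × time. This cannot be ruled out. But the article elsewhere uses study group and control group for the arms, and Analytical methods sets type of school beside course, as a descriptor.
- **The one-way factor is not stated to be time.** Asking whether main effects are sustained over time fits a group effect from step 1 better than a time effect, and the power statement concerns two groups. Against this, step 1 is introduced as comparing the three evaluations, and Tukey or Games-Howell comparisons suit a factor with three or more levels, which arm is not. The text is ambiguous.
- **The screen is worded as a sequence.** A reader might infer that the factorial model is run only on variables that pass step 1 and that all others are dropped. That is the natural reading, but the word only is not in the text.
- **The blinded-analyst arrangement and the power basis show that the groups are to be compared.** They show intent; they do not supply a model that does it.

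A reader might also infer that the plan will lose about 73% of real effects (100 − 27) or report false success in more than 99% of trials with shared drift. The documents do not support either as a property of the plan. The first figure holds only for an unpaired test over time, pooled over arms, at one assumed correlation; the second also needs an assumed drift of 0.2 SD.

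**Conclusion.** The point holds in this form: no analysis as written names the randomised arm or arm × time, so on the plain reading the main hypothesis is not tested. It would be too strong to say that the sponsor has certainly left the arm out, because type of school could loosely stand for it. Even on that kinder reading the text has to say so, the main-effects screen remains, and the factor of the one-way ANOVA is undefined.

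The direction of the harm is clear: shared change can pass for a programme effect, and a real effect can be screened out. Its size is conditional. For a true 0.2 SD effect, a pass rate of roughly 18 to 37% applies if step 1 is an unpaired ANOVA over time pooled over arms, with ρ assumed between 0.8 and 0.3 and clustering ignored. Because the trial's main objective is affected and the correction is nearly free, it should be made before the data are analysed.

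**What to change.** - Delete the one-way step and the main-effects screen.
- For every listed outcome, fit one repeated-measures mixed model with arm, visit (post-intervention and 3 months) and arm × visit, adjusted for the baseline score.
- Include school as the randomised cluster, as a random effect, with a small-sample degrees-of-freedom method suited to five schools per arm, and student as the repeated-measures effect. Arm, visit and arm × visit alone, without a school term, would give intervals that are too narrow under any positive school-level correlation.
- Report the baseline-adjusted arm difference with its confidence interval at post-intervention and at 3 months.
- Keep school-size block and grade as covariates only, and define type of school if the term is retained.

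Cost: a change of wording and slightly more analysis work. No new data are needed, since Table 2 schedules every outcome at baseline. The price is wider intervals, which are the honest ones for ten randomised schools.
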